# Effect of emerging digital technologies and methodologies combined with incentives on HbA1c in patients with type 2 diabetes mellitus: study protocol for a parallel, open randomized controlled trial

**DOI:** 10.1186/s13063-024-07950-z

**Published:** 2024-02-01

**Keywords:** Behavioral economics, Digital health, Type 2 diabetes mellitus

## Abstract

**Background:**

Type 2 diabetes mellitus (T2DM) is a common metabolic disease that requires long-term management and treatment. Digital intervention, as an emerging medical model, has been widely used in the treatment of T2DM patients. Behavioral economics theory provides a favorable perspective for studying the effect of digital intervention because it can reveal the decision-making mechanisms behind human behavior and provide more effective interventions for digital intervention. The purpose of this trial is to evaluate the impact of behaviorally based digital intervention on T2DM patients’ HbA1c, self-monitoring of blood glucose (SMBG) testing rate, diabetes self-efficacy, and other indicators compared to conventional treatment.

**Methods:**

This trial is a prospective randomized controlled trial conducted at the First People’s Hospital of Kunshan City from April 1, 2023, to December 31, 2024, with a follow-up period of 3 months. The specific randomization method was established and implemented through the EDC clinical trial center’s randomization system. We will measure and collect baseline data from three groups, including Group A: digital intervention + virtual incentives + conventional treatment, Group B: digital intervention + physical incentives + conventional treatment, and Group C: conventional treatment. HbA1c, weight, SMBG testing rate, diabetes self-efficacy, and diabetes-related medical expenses will be recorded at baseline, 1 month, 2 months, and 3 months for all three groups. The Shapiro-Wilk test will be used to test for normality, and Pearson correlation analysis will be used for correlation analysis. Dropouts will be analyzed separately. Analysis of variance or exact probability calculation will be used to compare demographic data and other baseline indicators.

**Discussion:**

This study is a novel clinical trial that integrates multiple disciplines (economics and medicine) and uses digital technology to deliver the intervention. Most published studies were offline interventions based on behavioral economics theory, but very few were on online interventions for T2DM patients. This study has both novelty and social value.

**Trial registration:**

Chinese Clinical Trial Registry ChiCTR2300070753. Registered on 2023/04/22.

**Supplementary Information:**

The online version contains supplementary material available at 10.1186/s13063-024-07950-z.

## Introduction

Diabetes is a common chronic disease with high-risk complications, resulting in a heavy medical burden. According to a recent report by the International Diabetes Federation (IDF), the number of adults aged 20–79 with diabetes in China is 140.9 million, accounting for about a quarter of the total number of people with diabetes worldwide; by 2045, this number will grow to 174.4 million, ranking first in the world [1]. Type 2 diabetes mellitus (T2DM) is the most common form of diabetes, accounting for approximately 90% of all cases. In 2019, direct health care expenditures due to T2DM have reached $760 billion [2]. The prevalence of T2DM has remained high for many years. Unhealthy diet and low physical activity appear to be the causal factors behind it [3]. Several studies have highlighted the role of lifestyle interventions in reducing the incidence and progression of T2DM [4, 5]. Effective lifestyle management in people with diabetes can help to delay progression, reduce the risk of complications, and improve quality of life. However, a lack of timely communication between doctors and patients reduces the continuity of intervention and monitoring, resulting in poor management of diabetic patients. Therefore, we are attempting to explore a new approach and method to provide efficient, continuous, and personalized lifestyle interventions for diabetic patients.

Digital healthcare is a new form and model that uses digital technology and information and communication technology (ICT) to improve healthcare [6], covering the entire healthcare process from prevention and early diagnosis to treatment and rehabilitation, including aspects of medical research, clinical practice, and patient management. Electronic medical record systems, medical imaging and diagnosis, mobile medical applications, and health management and monitoring are the main forms of digital health applications in healthcare. Some studies have shown that the adoption of mobile health apps has been a good driver in helping people with diabetes with diet, exercise, and lifestyle management [7, 8]. Another meta-analysis showed that mobile app-assisted self-care interventions had a significant effect on HbA1c levels, fasting blood glucose levels, and waist circumference control in patients with T2DM [9]. Overall, previous studies have shown that mHealth technology and platform design have great potential to achieve better healthcare outcomes.

The long-term treatment process of chronic diseases relies heavily on patient self-management. An observational study found that among various mobile applications, patients with T2DM exhibited the highest level of engagement only in monitoring daily physical activity using accelerometers [10]. This may be attributed to the passive nature of data collection and transmission through accelerometer-type devices. In this study, we propose for the first time the idea of designing medical applications using behavioral economics and cognitive behavior therapy (CBT) as methodological approaches to design medical applications in order to improve the attractiveness of everyday tasks and increase organizational effectiveness. Behavioral economics theory suggests that human decision-making and behavior are influenced by emotions and social factors, allowing designers to leverage these factors to influence human decision-making. Adding gamification design based on this theory can significantly improve patient engagement and compliance in digital therapy [11, 12]. Previous studies have shown that a small financial incentive coupled with a written reminder can increase patient participation at HbA1c screening [13]. The incentive setting of a reminder letter and a $6 gas card increased the average number of HbA1c tests for T2DM patients from 2.7 to 3.3 over 2 years [14]. CBT, on the other hand, helps mobile applications establish the correct system of cognition and behavior. Using this framework, we aim to investigate the effectiveness of incentive design mechanisms in gamification for managing patients with T2DM by comparing the effectiveness of monetary rewards and non-monetary rewards. This research will contribute to expanding the existing theories of gamified information systems.

Through this study, we aim to collect data on the health activities of patients with T2DM, such as step count and dietary habits, as well as changes in HbA1c levels, in order to elucidate the impact of a novel digital intervention approach on T2DM patients. Additionally, we will further explore the influence of incentive mechanisms on patients’ health behaviors.

### Evidence before this study

Diabetes is a chronic disease that seriously threatens the health of patients. However, the current management mode has a poor control rate for diabetes. Digital intervention is a new means of daily management, monitoring, and intervention of patients using digital monitoring technology and information communication technology. Gamification and social incentive measures are the main reasons why digital intervention platforms attract patients to use them [15]. We searched PubMed for studies using behavioral economics-based digital intervention in T2DM patients from November 2016 to December 2022. The search terms included T2DM, digital intervention, behavioral economics, and gamification. Medical subject headings (MeSH) were used to include synonyms. According to our search, some studies have shown that digital intervention is effective in strengthening diabetes self-management education and blood glucose control in adult T2DM patients [16]. However, almost no studies based on interdisciplinary theoretical integration have been published in the T2DM population. We identified two randomized controlled trials evaluating the effectiveness of digital intervention platforms in T2DM patients. The results showed that compared with the control group (*n*=120), the blood glucose control of patients in the digital monitoring group (*n*=120) was significantly improved during the follow-up period until the end of the study [17]. There was no difference in the number of adverse events and health-related quality of life between the two groups. Another multicenter randomized controlled trial found that for every additional day of mobile app use, the HbA1c level of participants (*n*=57) decreased by 0.016 points (95% CI: −0.03 to −0.003). However, the use of the application varied among the trial sites [18].

### Added-value of this study

Previous studies mainly focused on applying digital intervention platforms in hospitals to improve the blood glucose management of inpatients with diabetes by nurses and doctors. However, information on the impact of digital intervention on T2DM patients outside the hospital is limited. Our study aims to evaluate the effectiveness of behavior economics-based digital intervention on HbA1c, SMBG testing rate, and diabetes self-efficacy in T2DM patients. During the study, we added a reward mechanism. By comparing the effects of tangible and virtual incentives on patients’ SMBG testing rate and self-efficacy, we studied the effect of incentive design mechanism in gamification on managing T2DM patients.

## Materials and methods

### Objectives

Aim1: To assess the effect of behaviorally informed digital intervention on HbA1c levels, prevalence of SMBG detection, weight, diabetes self-efficacy, and diabetes-related expenses in patients with type 2 diabetes compared to standard treatment.

Hypothesis 1a: Evaluate the changes in HbA1c levels in the intervention and control groups. At 3 months, there will be significant differences in HbA1c levels prevalence of SMBG detection, weight, diabetes self-efficacy, and diabetes-related expenses among the three groups: A (digital intervention + virtual incentives + standard treatment), B (digital intervention + tangible incentives + standard treatment), and C (standard treatment).

### Study design and setting

This study is a single-center, randomized, controlled, open-label, parallel-group superiority trial. Patients were randomly assigned in a 1:1:1 ratio to evaluate the efficacy of behavioral economics-based digital intervention on HbA1c, SMBG testing rate, and diabetes self-efficacy in patients with T2DM. The study protocol followed the Standard Protocol Items: Recommendations for Interventional Trials (SPIRIT) guidelines [19]. This study will be conducted at the First People’s Hospital of Kunshan City, Jiangsu Province, China, from April 1, 2023 to December 31, 2024.

### Inclusion criteria

Patient inclusion criteria are as follows: (1) aged 18–65 years old; (2) diagnosed with T2DM according to the 1999 WHO criteria, and with a disease duration of > 6 months; (3) stable treatment for diabetes for ≥2 months (e.g., metformin ≥ 1000mg/day or maximum tolerated dose), with 7.0% ≤ HbA1c ≤ 10.5%; (4) able to use a smartphone without barriers and have basic Chinese literacy and simple arithmetic skills (education requirement: primary school graduation level and above); (5) voluntarily sign an informed consent form and agree to strictly follow the requirements of this protocol.

### Exclusion criteria

The exclusion criteria for patients are as follows: (1) use of traditional Chinese medicine or herbal medicine with hypoglycemic effects within 2 months prior to screening; (2) currently receiving chronic systemic corticosteroid therapy (> 2 weeks), or use of corticosteroids within 4 weeks prior to screening (except for topical, intraocular, intranasal, or inhaled administration); (3) occurrence of 2 or more episodes of ketoacidosis, hyperosmolar state, or lactic acidosis within 6 months prior to screening; (4) history of severe hypoglycemic events within 6 months prior to screening, defined as the presence of neurological symptoms of hypoglycemia that require assistance from others to recover, or previous lack of knowledge about hypoglycemia or inadequate understanding of hypoglycemic symptoms, and the researcher deems that the subject is unable to communicate and understand hypoglycemic symptoms and appropriate treatment should also be excluded from the study; (5) severe chronic complications of T2DM, such as diabetic foot; (6) history of acute or chronic pancreatitis; (7) previous or current proliferative diabetic retinopathy or diabetic macular edema requiring urgent treatment; (8) previously diagnosed autonomic neuropathy manifested as urinary retention, resting tachycardia, orthostatic hypotension, or diabetic diarrhea; (9) occurrence of acute myocardial infarction, unstable angina, coronary artery bypass grafting, percutaneous coronary intervention (excluding diagnostic angiography), transient ischemic attack, cerebrovascular accident, decompensated heart failure classified as NYHA class III or IV within 6 months prior to screening; (10) concomitant acute non-cardiac disease, such as infection, renal failure, and hyperthyroidism; (11) concomitant other severe cardiovascular diseases, including moderate to severe stenotic valvular heart disease, hypertrophic cardiomyopathy or other forms of outflow tract obstruction, acute myocarditis, pericarditis, active endocarditis, suspected or known ruptured aneurysm, and acute pulmonary embolism or pulmonary infarction; (12) concomitant neurological, muscular, skeletal, or rheumatic diseases that may worsen with exercise; (13) mental illness that cannot live independently or cooperate with treatment; (14) lactation, pregnancy, or planned pregnancy; (15) patients deemed unsuitable for inclusion in the study by the researcher.

### Interventions

To compare the effects of digital intervention based on behavioral economics theory on HbA1c, SMBG testing rate, and diabetes self-efficacy in patients with T2DM, conventional treatment was used as a control intervention. Conventional treatment was administered according to the T2DM conventional drug treatment method recommended by clinical guidelines. Conventional drugs include but not limited to metformin, sulfonylureas, glinides, α-glycosidase inhibitors, TZDS, DPP-4i, SGLT2i, GLP-1RA, and insulin. Digital intervention refers to the use of WeChat mini-program in smartphones to provide patients with out-of-hospital coordinated management based on cognitive behavioral therapy, guiding patients to improve their health behaviors in coping with diabetes and enhance the level of blood glucose self-management. The main content includes disease knowledge courses, auxiliary training courses (diabetic diet essentials), psychological counseling courses, course Q&A games, and relevant behavior records (daily attendance, medication check-ins, daily sugar control diet punch card). From day 1 to 1 month of the study is the first cycle, to 2 months is the second cycle and to 3 months is the third cycle.

After completing a single cycle of digital intervention, the subjects who receive digital intervention can receive virtual and tangible incentives respectively. On the first day of each cycle, the incentive content to be received at the end of the cycle will be reminded during follow-up. The subjects need to provide self-recorded and completed SMBG diaries to the researchers to receive incentives after check-in. The virtual incentive is a healthy behavior learning badge that lights up each cycle, including bronze, silver, and gold, which are awarded in turn according to the user’s completion (≥70%, ≥80%, ≥90%) judged by the researcher. The tangible incentive is a health behavior auxiliary tool provided each cycle, including an electronic medication box, a weight scale, and a smart bracelet, which are awarded in turn according to the user’s completion (≥70%, ≥80%, ≥90%) judged by the researcher.

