#### Secondary outcome measures

At the 3-month follow-up, the difference in SMBG testing rate among the three groups will be compared;At the 3-month follow-up, the difference in weight among the three groups will be compared;At the 3-month follow-up, the difference in diabetes self-efficacy among the three groups will be compared;At the 3-month follow-up, the difference in diabetes-related diagnosis and treatment expenses among the three groups will be compared.

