### Participant timeline

The schedule of the participants is shown in the Table 1.

**Table 1 Tab1:** The schedule of the participants

Period	Baseline screening	Follow-up period			
Interview	1	2	3	4	5
Days	-7~-1	1	28 ± 5	56 ± 5	84 ± 5
Informed consent	√				
Baseline characteristics	√				
Physical exams/urinalysis/ Kidney and liver functions	√				
H1Abc	√				√
Inclusion exclusion criteria review	√				
Random allocation		√			
Digital intervention^1^		√	√	√	√
Conventional therapy		√	√	√	√
Incentives^2^			√	√	√
SMBG testing rate^3^			√	√	√
Weight^4^			√	√	√
Scale evaluation^5^		√	√	√	√
Medical expenses^6^		√	√	√	√
Adverse events evaluation		√	√	√	√

(1) Digital intervention: implementation of the WeChat mini-applet. (2) Incentives: patients will be given incentive content at the end of each monthly follow-up. (3) Calculation of testing rate: self-blood glucose monitoring once every morning on an empty stomach, continuous monitoring for 3 months, detection rate = actual measurement times/expected measurement times, and data recorded in the SMBG diary card. (4) Weight: measured at the clinic during each follow-up visit. (5) Scale evaluation: completed the scale evaluation under the doctor’s instructions. (6) Diagnosis and treatment expenses: during the 3-month period, all medical expenses related to diabetes diagnosis and treatment, including outpatient and inpatient visits, will be recorded

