### Recruitment

We will recruit patients at the First People’s Hospital of Kunshan in Jiangsu Province, China. Once recruited, the study staff will guide patients through the process of learning digital intervention operations/diary card recording, and confirm the content and frequency of digital intervention and the requirements for diary card recording with the patients.

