### Sequence generation

In this randomized controlled trial, a simple randomization method was used to allocate participants to three groups with a 1:1:1 allocation ratio. Group A: digital intervention + virtual incentives + conventional treatment, Group B: digital intervention + physical incentives + conventional treatment, and Group C: conventional treatment. A central randomization system for the EDC clinical trial is established and implemented. Randomizers at the trial center will access the system with an account number and password, enter basic information about the subject patients and generate a randomization number for follow-up.

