Missing values will not be replaced or added. All analyses will be based solely on observed cases. Patients lost to follow-up will be considered to have dropped out of treatment. Only PP patients will be used in sensitivity analyses to test the impact of this assumption. No genetic or molecular analysis will be performed in this trial or future use.

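### The SMBG testing rate rests on a self-written diary whose return is rewarded in Groups A and B but not in C, so the comparison mixes testing with recording

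*Protocol article*

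**What the plan says.** Secondary outcome measures (Protocol article) lists the comparison: "At the 3-month follow-up, the difference in SMBG testing rate among the three groups will be compared". Note 3 to Table 1, under Participant timeline, asks for one fasting reading each morning for three months and defines the rate: "detection rate = actual measurement times/expected measurement times, and data recorded in the SMBG diary card". No other source for the count is named.

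Interventions sets the reward condition: "The subjects need to provide self-recorded and completed SMBG diaries to the researchers to receive incentives after check-in". The same section limits who can earn a reward: "the subjects who receive digital intervention can receive virtual and tangible incentives respectively". The reward is a badge in Group A and a physical item in Group B. Sequence generation gives the third arm as "Group C: conventional treatment", with no incentive.

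Assignment of interventions states that participants and investigators know the allocation. On missing data, Statistical methods rules out replacement of missing values and adds: "All analyses will be based solely on observed cases". The article has no rule specific to diary cards.

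**The concern.** One document does two jobs. The diary card is the source of the outcome and, in two arms of three, the thing a patient must hand over to be rewarded. A patient in A or B who missed readings has a motive to fill in the gaps before the visit; a patient in C has no such motive. A higher recorded rate in A or B could then mean more testing, fuller recording, or both, and the diary cannot tell them apart.

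A second mechanism may work against the first. If poor testers in C return fewer cards and those cards drop out, the observed rate in C is too high and a real effect is partly hidden.

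The outcome is secondary, but it matters to the trial's question: the section on the added value of the study names the effect of tangible against virtual incentives on the SMBG testing rate as something the trial will compare.

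**Working it through.** **Plan's own figures.** The article gives no expected SMBG rate, SD or sample size for this outcome. Its one sample-size figure, 100 per group with 20% dropout, is for HbA1c. It is used here only to get an analysable number: 100 × (1 − 0.20) = 80 per arm. Every rate, return share and SD below is an assumption.

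**Step 1, over-recording in A and B.** Assume a true rate of 60% in every arm, so there is no real effect. If a share f of untested days is filled in, the reported rate is 0.60 + f × (1 − 0.60). The last column is the chance that a two-sided 5% test of one rewarded arm against C is significant, with SD 0.25. The standard error is 0.25 × √(2/80) = 0.0395, and the chance is approximately Φ(difference/0.0395 − 1.96).

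| f | Reported rate, A or B | Spurious difference from C | Chance of significance |
|---|---|---|---|
| 0.05 | 62% | +2 points | not computed |
| 0.10 | 64% | +4 points | 0.17 |
| 0.20 | 68% | +8 points | 0.53 |
| 0.30 | 72% | +12 points | 0.86 |

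For SDs of 0.20 to 0.30 the last three chances range over 0.13–0.24, 0.39–0.72 and 0.72–0.97.

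**Step 2, selective return in C.** Assume half of each arm tests on 80% of days and half on 40% (mean 60%), and that all A and B cards come back without over-recording.

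- C returns 80% of cards (95% of high testers, 65% of low). Observed cases: (0.95 × 0.80 + 0.65 × 0.40)/(0.95 + 0.65) = 1.02/1.60 = 63.75%, so A or B minus C is about −4 points. Unreturned cards as zero: 1.02/2 = 51%, so the difference is +9 points.
- C returns 70% (90% and 50%). Observed cases: (0.72 + 0.20)/1.40 = 65.7%, difference −5.7 points. As zero: 0.92/2 = 46%, difference +14 points.

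**Step 3, both together.** Suppose 70% of C return cards showing 80%, and the other 30% in truth test on 30% of days. The true C rate is 0.7 × 0.80 + 0.3 × 0.30 = 65%. Let A or B share that true rate and over-record by 10 points, to 75%, with all cards returned.

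- Observed cases: C reads 80%, difference 75 − 80 = −5 points.
- Unreturned cards as zero: C reads 0.7 × 0.80 = 56%, difference 75 − 56 = +19 points.

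The true difference is nil in both lines. The sign of the error depends on how unreturned cards are scored, and zero-scoring adds to the over-recording bias.

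**The case against.** Several points on the other side stand.

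- **Incentives are meant to raise testing.** A difference need not be artefact. The point is only that the diary cannot separate the two.
- **Group C is not left out of diary collection.** Table 1 schedules the SMBG rate at days 28, 56 and 84 with no restriction by arm. Under Recruitment, staff "confirm the content and frequency of digital intervention and the requirements for diary card recording with the patients", again without naming arms. Patients agree to follow the protocol, attend for weighing and are telephoned when data are missing. A reader might infer that C has no reason to return a card; the text supports only that C lacks the reward.
- **Blank days already count.** The denominator is expected readings, so a day without an entry lowers the rate. Only a wholly absent card is unscored.
- **Unreturned cards are not expressly called missing.** A reader might take that as a stated rule. It follows only by applying the general observed-case sentence, and the full protocol or SAP may say more.
- **Card return can be seen.** Missing data are detected in the EDC, so return can be counted by arm. Over-recording cannot be seen.
- **A versus B is less certain.** The diary condition is identical in both arms, and that goods prompt more filling-in than badges is conjecture. The 70%, 80% and 90% completion thresholds are not said to refer to diary entries, so nothing here rests on them.

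The Discussion concedes possible bias from lack of blinding, but not this link between reward and record. None of these points supplies a source for the count that is independent of the rewarded document.

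**Conclusion.** The concern holds as a measurement problem in one secondary outcome. What the article fixes is enough to show it: an unverified diary as sole source, a reward for handing it in confined to A and B, and open allocation. As planned, a difference between a rewarded arm and C cannot be read as a difference in testing alone; A versus B may also be affected.

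On the assumed inputs, over-recording gives +2 to +12 points and selective return in C under observed cases gives about −4 to −6. These show plausible size; they are not estimates. A reader might infer that the plan favours the digital arms, or that it hides their effect. The documents support neither, because the two mechanisms oppose each other and neither is quantified. HbA1c is not taken from the diary, so the primary comparison is untouched by this mechanism.

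**What to change.** 1. In all three arms, at the day 28, 56 and 84 visits, take the numerator from the meter's time-stamped memory where the patient's meter stores it. Keep the same expected-reading denominator. Use the diary only where no meter record exists.
2. Report by arm the source of the count and the share of cards returned.
3. Where no meter data exist and the card was never returned, analyse it both as missing and as not tested, and show both results. They bracket the effect of non-return only if non-returners test no more often than returners, and they do not address over-recording. Do not use zero-scoring as the sole rule.
4. Call the result diary-recorded testing where no meter data exist.

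The cost is about a minute per visit and a change to the outcome definition. Meter data will be incomplete, since the article does not say which meters patients use, and the outcome will mix two sources. The reward scheme itself need not change.
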